### Data quality assurance plan

Several strategies have been implemented to reduce data errors, including a limited number of open questions, a predefined range of values where applicable, an easy-to-use case report form build that uses branching logic to reduce fields to complete, one person per site assigned to data collection, correction of systematic inconsistencies and verification of outliers. The different forms that will be used to collect the data in a systematic way are shown in appendix 1.

### Heterogeneity tests

Populations from diverse genetic, socio-cultural and socio-economic backgrounds can be quite different in their characteristics. Additionally, there may be some disparities between sites with respect to the quality and quantity of data items that each site can measure. This is expected regarding a data collection that allows any site to contribute. Consequently, heterogeneity in effect estimates may be due to clinical differences between pregnant women and/or site-level differences in terms of exposure and outcome determination (reporting or assessment bias). We will formally assess heterogeneity taking into account variations in exposure, covariates, and significant outcomes, and use meta-analysis methods (Q or I statistics, meta-regression, and subgroup analysis) to unravel heterogeneity at central and individual levels. Briefly, we will incorporate individual-level interaction terms in one-stage analysis and random intercepts to account for central-level factors not measured in the regression models mentioned above.

## EXTRACTION OF DATA FROM THE REGISTRY: SUBSTUDIES

Based on the registry prepared, data extraction will be carried out to carry out four sub-studies that address the secondary objectives.

### Substudy 1: Prospective observational study on delivery and vertical transmission to the new-born.

#### Objective/s

1. Determine the variables that are associated with more maternal and neonatal morbidity.
2. Determine if there is vertical transmission.
3. Evaluate the risk of SARS-CoV-2 infection during pregnancy.
4. Characterize the clinical course of SARS-CoV-2 infection during delivery
5. Identify additional risk factors and risk modifiers (e.g., symptomatic infection, SARS-CoV-2 positive amniotic fluid, co-infections).

#### Design

Prospective observational study in 100 Spanish sites

Recruitment: 1st March 2020 to 1st March 2021. Spanish sites collected in Appendix 1.

#### Patients

Patients eligible for follow-up or target population will be any pregnant woman who is suspected of or needs to be ruled out as having SARS-CoV-2 infection at any time during pregnancy with positive test results for SARS-CoV-2 by PCR.

The result of the PCR test on a sample of nasopharyngeal and/or oropharyngeal swab was considered synonymous with exposure/non-exposure, defining a case as any pregnant woman with a positive result, regardless of the symptoms. Those cases with clinical presentation of COVID19 were classified according to the WHO division for adults into: mild symptoms, mild-moderate pneumonia, severe pneumonia and septic shock (16).

The recommended samples for diagnosis are samples from the upper respiratory tract: nasopharyngeal and/or oropharyngeal swab.

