## Study design

Prospective observational registry study of pregnant women with suspected SARS-CoV-2 infection at any time during pregnancy with positive test results for SARS-CoV-2.

A specific database will be developed, which will include the baseline characteristics of the pregnant women, aspects related to the course of pregnancy and childbirth, and the new-born. Vertical transmission will be analysed only by means of a nasopharyngeal swab from the new-born before contact with the mother. This registry sets an observation deadline of up to 14 days after birth for the new-born and 6 weeks postpartum for the mother. The registry will be hosted on a secure https server, this server will be physically located at **OBS Covid Spain** of the company ReserArch which has a contract with the Puerta de Hierro-Majadahonda University Hospital Research Foundation.

Recruitment period will be between 1st March 2020 and 1st March 2021.

After that, different sub-analyses will be carried out with the data extracted in the registry and the secondary objectives will be addressed.

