### Definitions of symptomatic and asymptomatic patient

- Acute symptomatic patient: Positive PCR. Manifests any of the symptoms compatible with COVID-19 at the time of the study or analysis or during admission. These symptoms may vary based on new findings.
- Symptomatic patient: Patients with symptoms before 14 days of delivery, even if they no longer have symptoms at the time of delivery.
- Asymptomatic patient: Positive PCR. No symptoms compatible with COVID-19 were observed at the time of the study or analysis.
- Ex-symptomatic or cured patient: Positive or negative PCR. The patient was symptomatic (PCR+) more than 14 days before delivery and no longer has any of the symptoms compatible with COVID-19 at the time of the study or analysis. Patient can be IgM positive or negative, but shall be IgG+ if serology is available
- Symptomatic patient with sequelae: Positive or negative PCR. The patient was symptomatic (PCR+) and has any of the sequelae recognized after COVID-19 at the time of data analysis. These sequelae may vary based on new findings.

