#### Primary variables

##### Maternal characteristics

|                                                                        |                           |
|------------------------------------------------------------------------|---------------------------|
| Age, mean years (range)                                         |                           |
| Age groups, n (%)                                               | <20                       |
|                                                                        | 20-34                     |
|                                                                        | ≥35                       |
| Time between COVID-19 diagnosis and delivery, mean days (range) |                           |
| Symptomatology, n (%)                                           | Showing COVID-19 symptoms |
|                                                                        | Asymptomatic              |

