##### Delivery characteristics

|                                                 |                    |
|-------------------------------------------------|--------------------|
| Gestational age, mean weeks (range)      |                    |
| Preterm deliveries (<37 weeks), n (%) |                    |
| Start of delivery, n (%)                 | Spontaneous        |
|                                                 | Induced            |
|                                                 | Elective caesarean |

|                                                     |                                           |
|-----------------------------------------------------|-------------------------------------------|
| Type of delivery, n (%)                      | Normal                                    |
|                                                     | Instrumental                              |
|                                                     | Caesarean                                 |
| Weight at birth, mean grams (range)          |                                           |
| Neonatal tests for COVID-19, n (%)           | <12 hours from delivery (Positive ones)   |
|                                                     | 12–48 hours from delivery (Positive ones) |
| Skin-to-skin within first 24 hours, n (%)    |                                           |
| Breastfeeding at immediate postpartum, n (%) |                                           |
| Arterial pH, mean value (range)              |                                           |
| 5-minute Apgar score, n (%)                  | <5                                        |
|                                                     | ≥5                                        |
| ICU admission, n (%)                         |                                           |

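### Substudy 1 reports newborn swab positives as one percentage over mothers infected at any time in pregnancy; it should be split by diagnosis-to-delivery interval

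*Protocol*

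**What the plan says.** **Population.** The Patients section of Substudy 1 admits women suspected of, or being ruled out for, "having SARS-CoV-2 infection at any time during pregnancy with positive test results for SARS-CoV-2 by PCR". The same section fixes the case definition by "defining a case as any pregnant woman with a positive result, regardless of the symptoms". Neither sentence requires a positive test at or near delivery.

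**Objective and measure.** One objective of Substudy 1 reads "Determine if there is vertical transmission". The Study design section states: "Vertical transmission will be analysed only by means of a nasopharyngeal swab from the new-born before contact with the mother".

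**Reporting.** The Delivery characteristics table of Substudy 1 has a row for neonatal COVID-19 tests, given as n (%). It has two time bands, "<12 hours from delivery (Positive ones)" and 12–48 hours. Each band covers the newborns of all mothers together.

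**Timing of maternal infection.** The Maternal characteristics table lists "Time between COVID-19 diagnosis and delivery, mean days (range)". The Statistics section of Substudy 1 plans descriptive summaries and unadjusted association tests. It does not use this interval to form a denominator, a stratum or a covariate.

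**Recovered women.** The Definitions section expects them: "Ex-symptomatic or cured patient: Positive or negative PCR", with the explanation "The patient was symptomatic (PCR+) more than 14 days before delivery and no longer has any of the symptoms". Substudy 1 neither excludes this group nor separates it.

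**The concern.** A swab at birth looks for virus present around delivery, while the enrolled population covers infection at any point in the preceding months. A woman who recovered well before delivery may carry no virus when her baby is born. If her newborn is swabbed and counted, it adds to the denominator with little chance of adding to the numerator.

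Two things follow. First, the reported percentage depends on how many early infections were enrolled and swabbed, as well as on the transmission risk. Second, a negative swab means different things in the two groups. After infection near delivery it is evidence about peripartum transmission. After an early infection it says little, because an in-utero infection could have cleared before birth.

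The percentage is likely to be read as the risk for a baby born to a woman who is infected at delivery. A low or zero pooled figure could then reassure more than the data allow. The Abstract and the Rationale both name vertical transmission among the effects for which accurate risk estimates are wanted, so the percentage will be read as a risk.

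**Working it through.** Substudy 1 states no sample size, expected transmission rate or precision, so there is no planned figure to reproduce. The only sample size in the protocol, 1056, belongs to Substudy 4 and has no bearing here.

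**Step 1: the passages side by side.** The exposure window is the whole pregnancy (Substudy 1, Patients). The outcome window is birth, before contact with the mother (Study design). The interval that links them is recorded but only summarised (Maternal characteristics). Elsewhere the protocol does tie the maternal PCR to delivery: controls need a negative test at delivery or less than 3 days before, and Substudy 4 asks for a test within 72 hours before or 24 hours after delivery.

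**Step 2: what the pooled percentage estimates.** Among newborns actually swabbed, let

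- f = share whose mothers were infected near delivery,
- r = swab-positive rate in that group,
- q = swab-positive rate in newborns of mothers infected earlier and since cleared.

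Pooled rate = f × r + (1 − f) × q. It lies below r whenever q < r and f < 1. With q = 0 it is f × r, so the dilution factor is f whatever the value of r. The protocol gives none of f, r or q; all values below are assumptions.

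| Assumed f | Pooled rate if r = 3%, q = 0 |
|---|---|
| 1 | 3% |
| 0.75 | 0.75 × 3% = 2.25% |
| 0.50 | 0.50 × 3% = 1.5% |
| 0.25 | 0.25 × 3% = 0.75% |
| 0.05 | 0.05 × 3% = 0.15% |

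The last row corresponds to infection dates spread evenly over an assumed 280-day pregnancy with a 14-day window (14/280 = 0.05). It is an extreme case: testing at delivery raises f, and women who delivered soon after recruitment opened on 1 March 2020 had little opportunity for infection months earlier. Taking q = 0 is also the extreme case. With q = 1% and f = 0.50, the pooled rate is 0.5 × 3% + 0.5 × 1% = 2%.

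Over r = 1% to 5% and f = 0.05 to 0.75, with q = 0, the pooled rate runs from 0.05 × 1% = 0.05% to 0.75 × 5% = 3.75%.

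**Step 3: the yes/no question.** Assume 200 swabbed newborns, r = 1%, q = 0 and f = 0.5.

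- Pooled: P(at least one positive) = 1 − (1 − 0.005)^200 = 63.3%.
- Restricted to the 100 newborns of women infected near delivery: 1 − (1 − 0.01)^100 = 63.4%.

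Restriction removes negatives only and leaves the positives where they were. The chance of seeing a transmission is the same.

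**Step 4: what a zero result would claim.** With no positives among n newborns, the upper limit of the exact two-sided 95% interval is 1 − 0.025^(1/n). For all 200 newborns this is 1.8%. For the 100 with mothers infected near delivery it is 3.6%. Under these assumed numbers, the pooled analysis would exclude risks that the relevant 100 newborns cannot exclude.

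**The case against.** **The objective is existence, and no rate estimator is defined.** This is correct, and a reader might infer from the mismatch that Substudy 1 is less able to detect transmission. The documents do not support that. Step 3 shows that restriction gains nothing for the yes/no question when the same women are enrolled. The concern survives only for the percentage that the table reports.

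**Newborns of recovered mothers may not be in the denominator.** The section on safety measures and confidentiality says that the recorded tests are those each site performs under its own protocol, with none added for the study. If sites mainly swab newborns of currently positive mothers, f is close to 1 and the dilution is small. It would therefore be wrong to state that every recovered woman's newborn dilutes the rate. The reply is limited: the share would then depend on local practice, which is a further reason to state the denominator and show the interval.

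**The broad population is deliberate.** The background section on vertical transmission covers transmission before, during and after delivery, and the Rationale asks for evidence on the first and second trimesters. Making the last 14 days the primary set would narrow that question. This stands, and it favours reporting by interval over restriction.

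**The protocol has no 14-day rule for PCR.** A reader might take the 14 days in the Definitions section as a ready-made cut. It refers to when the woman had symptoms, gives no rule for asymptomatic women, and allows a positive PCR in the recovered group. A woman diagnosed 20 days before delivery, still infected but not retested, would fall outside such a window.

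**An analysis plan may handle this.** The Study design section announces sub-analyses, and the section on heterogeneity mentions subgroup analysis and interaction terms, although mainly for site and population differences. A plan that is not shown may already stratify by interval, which is a reason to rate the point modestly.

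**The objective on the clinical course during delivery** might seem to share the fault. It limits itself in time, and its table heads the mild symptoms as those reported at birth, so the point is not extended to it.

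**Conclusion.** The mismatch is real but limited. As the protocol stands, the newborn swab percentage in Substudy 1 mixes mothers infected near delivery with mothers infected at any earlier time. To the extent that newborns of cleared mothers are swabbed and are positive less often, it understates the rate for women infected near delivery and varies with the mix of diagnosis dates. A negative swab after an early infection cannot be read as absence of transmission.

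The size cannot be derived from the document. The halving of an assumed 3% to 1.5% holds only if half of the swabbed newborns had mothers whose infection had cleared and none of those newborns tested positive. The yes/no objective is not materially affected, and nothing shows that the broad population is an error. This is a cheap improvement, not a flaw that undermines the substudy.

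**What to change.** In the variable tables and Statistics section of Substudy 1:

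1. Report newborn swab positives over newborns tested, with 95% confidence intervals, by pre-stated diagnosis-to-delivery interval. Show the number not tested in each interval.
2. Give women PCR-positive close to delivery their own stratum and show earlier infections as separate rows. The sponsor should choose and justify the window, stating it as its own choice rather than borrowing the symptom-based 14 days.
3. Draw any conclusion about women infected at delivery from that stratum only. State that a negative swab after an earlier infection does not rule out transmission.

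The diagnosis-to-delivery interval is already collected, so the change needs wording and one derived grouping. The price is smaller strata and wider confidence intervals. Fixing the intervals now also prevents a denominator from being chosen after the results are known.

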#### Primary variables

##### Maternal characteristics

|                                                                        |                           |
|------------------------------------------------------------------------|---------------------------|
| Age, mean years (range)                                         |                           |
| Age groups, n (%)                                               | <20                       |
|                                                                        | 20-34                     |
|                                                                        | ≥35                       |
| Time between COVID-19 diagnosis and delivery, mean days (range) |                           |
| Symptomatology, n (%)                                           | Showing COVID-19 symptoms |
|                                                                        | Asymptomatic              |

##### Delivery characteristics

|                                                 |                    |
|-------------------------------------------------|--------------------|
| Gestational age, mean weeks (range)      |                    |
| Preterm deliveries (<37 weeks), n (%) |                    |
| Start of delivery, n (%)                 | Spontaneous        |
|                                                 | Induced            |
|                                                 | Elective caesarean |

|                                                     |                                           |
|-----------------------------------------------------|-------------------------------------------|
| Type of delivery, n (%)                      | Normal                                    |
|                                                     | Instrumental                              |
|                                                     | Caesarean                                 |
| Weight at birth, mean grams (range)          |                                           |
| Neonatal tests for COVID-19, n (%)           | <12 hours from delivery (Positive ones)   |
|                                                     | 12–48 hours from delivery (Positive ones) |
| Skin-to-skin within first 24 hours, n (%)    |                                           |
| Breastfeeding at immediate postpartum, n (%) |                                           |
| Arterial pH, mean value (range)              |                                           |
| 5-minute Apgar score, n (%)                  | <5                                        |
|                                                     | ≥5                                        |
| ICU admission, n (%)                         |                                           |

#### Evaluation 14 days after delivery, N

|                                                   |                                 |
|---------------------------------------------------|---------------------------------|
|                                                   |                                 |
| Symptomatology, n (%)                      | Showing COVID-19 symptoms       |
|                                                   | Asymptomatic                    |
| COVID-19 symptoms                          |                                 |
| Mild symptoms (Symptoms reported at birth) | Cough                           |
|                                                   | Fever                           |
|                                                   | Dyspnoea                        |
|                                                   | New olfactory or taste disorder |
|                                                   | Fatigue/malaise                 |
|                                                   | Altered consciousness           |
|                                                   | Headache                        |
|                                                   | Nausea/vomiting                 |
|                                                   | Diarrhoea                       |
| Mild-moderate pneumonia                    |                                 |
| Severe pneumonia                           |                                 |
| Septic shock/maternal mortality            |                                 |

The rest of the variables are defined in appendix 5

### **Statistics**

For the statistical analysis, the SAS v9.4 software will be used.

The set of groups of variables requested and collected for each enrolled patient will be the same. The demographic and clinical characteristics of the population included will be summarized. Mean, standard deviation, minimum and maximum or median and interquartile intervals will be used for continuous variables, according to the distribution. The corresponding absolute and relative frequency will be reported for the discrete variables.

An analysis of the possible association of both the characteristics of the patients and the outcomes collected with COVID-19 infection will be carried out using Pearson's Chi-square test or Fisher's exact test and the Mann-Whitney U test (after verification of the absence of normal data by the Kolmogorov-Smirnov test). See section on Data Quality Plan and sample size. Statistical significance was established with  $P < 0.05$ .

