### Clinical course of SARS-CoV2 infection in pregnant women

Pregnant women are known to experience immunological and physiological changes that can make them more susceptible to viral respiratory infections, including COVID-19. Several studies revealed that pregnant women with different viral respiratory diseases had a high risk of developing obstetric complications and adverse perinatal outcomes compared to non-pregnant women, due to changes in immune responses (3,4). We also know that pregnant women may be at risk of serious illness, morbidity, or mortality compared to the general population, as seen in other coronavirus infections.

Coagulation alterations have been described in people admitted to hospital for COVID-19 and, given that pregnancy confers a state of hypercoagulability, it is to be assumed that SARS-CoV2 infection in pregnant women may increase the risk of suffering from thromboembolic events, therefore, depending on the symptoms and other risk factors, they would require heparin prophylaxis (5,6). In Spain, there have been two deaths of patients with COVID-19 who had completed their pregnancies by Caesarean section, although it should be borne in mind that in both cases the Caesarean section was carried out due to severe maternal involvement (7). The causes of these deaths were related to coagulation abnormalities, in the first case due to pulmonary thromboembolism in a context of sepsis and in the second due to abruptio placentae with fulminant coagulopathy (8).

Regarding the period of gestation, no significant differences have been found between the course of the disease depending on the trimester of gestation, although most admissions for COVID-19 have occurred during the second and third trimesters (5,6,9). However, it has been shown that caesarean delivery is an independent risk factor that increases the chances of clinical worsening in pregnant women compared to vaginal delivery (7), both in asymptomatic pregnant women and in those with mild symptoms.

In China, several published studies show that in cases where the pregnant woman had pneumonia or a diagnosis of SARS-CoV-2, the delivery was often completed by caesarean section. The results of the Chinese series on 18 published cases show that 16 have resulted in caesarean section and two in vaginal deliveries. In these series, the patients showed symptoms of the disease (fever and cough) before, during and after delivery (10,11).

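### Substudies 1 and 2 look for variables associated with morbidity but specify only unadjusted two-group tests, which cannot separate delivery factors from the illness that led to them

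*Protocol*

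**What the plan says.** The first objective of both Substudy 1 and Substudy 2 is to "Determine the variables that are associated with more maternal and neonatal morbidity". Both also aim to identify additional risk factors and risk modifiers.

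The Statistics sections of the two substudies give descriptive summaries and then a single inferential sentence. It relates patient characteristics and recorded outcomes to infection status, and on method it states only that this "will be carried out using Pearson's Chi-square test or Fisher's exact test and the Mann-Whitney U test". The significance threshold is P < 0.05. Neither section mentions regression, stratification or adjustment.

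Both substudies take women suspected or tested "at any time during pregnancy with positive test results for SARS-CoV-2 by PCR".

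Substudy 1 lists under Maternal characteristics a binary symptom item ("Showing COVID-19 symptoms" or asymptomatic), and under Delivery characteristics the start and type of delivery. Its next table, on the evaluation 14 days after delivery, covers symptoms, pneumonia grade and septic shock or maternal death.

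On the two maternal deaths it cites, the background section on clinical course says that "it should be borne in mind that in both cases the Caesarean section was carried out due to severe maternal involvement".

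**The concern.** A woman who is already seriously ill is more likely to be delivered by caesarean or early, and more likely to get worse afterwards. A crude comparison of delivery types credits the delivery with part of the effect of the illness. The result can be an apparent risk factor with no effect of its own, or a real effect that is hidden. Two-group tests also cannot show which of several correlated characteristics matters, and they cannot test effect modification, which both substudies name as an aim.

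The registry is intended to help set and monitor measures of care, so a misattributed delivery effect could reach practice. The background section already describes caesarean as an independent risk factor for worsening in asymptomatic and mildly ill women. Independence is a claim about adjusted effects, and crude tests can neither confirm nor refute it.

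**Working it through.** **No figure to reproduce.** Substudies 1 and 2 state no sample size, power or effect size. The first step is therefore to compare the sections.

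| Section | Inferential method | Adjusted predictors of morbidity among infected women? |
|---|---|---|
| Substudy 1, Statistics | Chi-square/Fisher, Mann-Whitney | No |
| Substudy 2, Statistics | Same | No |
| Substudy 3, Statistics | Multiple logistic regression | No: only the COVID odds ratio is interpreted; other variables are declared irrelevant |
| Substudy 4, Statistics | Univariate and multivariate logistic regression | No: a prevalence study that excludes women positive before delivery |
| Heterogeneity tests | Meta-analysis methods, meta-regression, subgroups; interactions and site random intercepts in regression models said to be mentioned earlier | No: no model precedes it and no severity covariate is named |

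No other section supplies the analysis missing from Substudies 1 and 2.

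**Illustration of size.** All rates are assumptions, because the documents give none. Let s be the share of women ill before delivery, c1 and c0 the caesarean rates in ill and other women, and m1 and m0 their risks of worsening. Within each severity group the caesarean odds ratio is set to 1.

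- P(C) = s·c1 + (1−s)·c0
- Risk after caesarean = [s·c1·m1 + (1−s)·c0·m0] / P(C)
- Risk after vaginal delivery = [s(1−c1)·m1 + (1−s)(1−c0)·m0] / [1−P(C)]

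Example A, with s = 0.15, c = 0.60 and 0.25, m = 0.25 and 0.03:

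- P(C) = 0.15×0.60 + 0.85×0.25 = 0.3025
- Risk after caesarean = (0.09×0.25 + 0.2125×0.03)/0.3025 = 0.0955
- Risk after vaginal delivery = (0.06×0.25 + 0.6375×0.03)/0.6975 = 0.0489
- Crude odds ratio = (0.0955/0.9045)/(0.0489/0.9511) = 2.05

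The last column below is the chance of P < 0.05 with 1000 women (an assumed number). It uses a two-sided normal approximation with pooled null variance, which corresponds to Pearson's chi-square.

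| Scenario | s | c1 / c0 | m1 / m0 | Risk C / V | Crude OR | P < 0.05 |
|---|---|---|---|---|---|---|
| Weak | 0.10 | 0.40 / 0.25 | 0.15 / 0.05 | 0.065 / 0.058 | 1.13 | 7.5% |
| B | 0.50 | 0.50 / 0.25 | 0.10 / 0.02 | 0.073 / 0.052 | 1.44 | 29% |
| Moderate | 0.10 | 0.60 / 0.25 | 0.30 / 0.05 | 0.103 / 0.064 | 1.67 | 55% |
| Moderate, more ill | 0.20 | 0.60 / 0.25 | 0.30 / 0.05 | 0.144 / 0.079 | 1.95 | 86% |
| A | 0.15 | 0.60 / 0.25 | 0.25 / 0.03 | 0.096 / 0.049 | 2.05 | 77% |
| Strong | 0.20 | 0.80 / 0.25 | 0.40 / 0.02 | 0.189 / 0.044 | 5.09 | >99% |

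With 500 women, A gives 50% and B gives 17%. Adjusting for the true severity returns an odds ratio of 1, but only because the example is built that way.

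**What the binary symptom item would remove.** Take A, suppose all ill women are symptomatic, and stratify on symptomatic versus asymptomatic. If 30% of women are symptomatic, half of that stratum is ill (0.15/0.30). The Mantel-Haenszel sums over the symptomatic and asymptomatic strata are then:

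- numerator 0.01214 + 0.00382 = 0.01596
- denominator 0.00636 + 0.00382 = 0.01018
- odds ratio 1.57

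With 50% symptomatic it is 1.83, and with 70% it is 1.96, against 2.05 crude. The binary item therefore removes only part of the bias.

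**The case against.** - **No crude test of delivery type against worsening is written.** This is correct. The tests relate variables to COVID-19 infection, so a reader who infers that the protocol plans a caesarean-versus-worsening test goes beyond the text. But with only PCR-positive women enrolled, the written tests have no uninfected group and do not address the morbidity objective. Redirecting them cures that defect and leaves this one.
- **The intent is descriptive.** Substudy 2 is labelled descriptive, the protocol says registry studies generally involve no hypotheses, and association need not mean cause. This has some force and is why restricting the objectives is an acceptable remedy. It does not fit with seeking risk factors and modifiers at P < 0.05.
- **The analysis plan may add a model.** It may. But this protocol fixes the method substudy by substudy, and names regression for Substudies 3 and 4 but not for 1 and 2.
- **The heterogeneity section provides regression tools.** It covers interactions, subgroups and meta-regression, so it would be wrong to call the whole protocol unadjusted. It refers, however, to models that appear nowhere before it.
- **Pre-delivery severity may not be available.** This stands in part. The symptom item under Maternal characteristics has no time point. The list headed "Mild symptoms (Symptoms reported at birth") sits under an evaluation 14 days after delivery. The WHO class is undated, and the variable list in Appendix 5 is a separate file.
- **Forcing severity into every model would do harm.** This stands. Age, BMI or comorbidity may act through severity, and gestational age at delivery may mediate neonatal outcomes. NICU admission is an outcome in this protocol, not a delivery factor.

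**Conclusion.** The point holds for the Statistics sections of Substudies 1 and 2. Their stated methods cannot meet the aims of finding variables associated with morbidity and identifying risk modifiers, and no other section fills the gap. For delivery factors, the background section supports the direction of confounding. That support is limited: the remark quoted concerns two deaths.

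The size cannot be derived from the documents. The assumed scenarios run from an odds ratio of 1.13, with a false-positive rate near nominal, to 5.09, where the crude test is almost always significant. They illustrate and do not bound the effect. A reader might take one of the middle scenarios as the expected bias, or expect that adjusting for symptom status would remove it entirely. The documents support neither inference. This is a change that should be made; it is not evidence that a particular result will be wrong.

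**What to change.** In the Statistics sections of Substudies 1 and 2:

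- Keep the two-group tests as description, directed at morbidity rather than infection.
- Name the morbidity outcomes, with NICU admission among them. Base conclusions on a multivariable logistic model for each, with the site random intercept from the Heterogeneity tests section.
- For delivery factors and maternal worsening after delivery, adjust for symptom status or WHO class fixed before delivery, and for age, BMI, comorbidity and gestational age.
- For baseline factors (age, BMI, comorbidity), adjust for the other baseline characteristics only, not for severity or gestational age at delivery.
- Test the named risk modifiers with interaction terms.
- Date the severity items, and use only those recorded before delivery. If only the binary symptom item is available at that time, state that residual confounding remains.

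The cost is a few sentences in two sections and more modelling. Symptoms, WHO class, age, BMI, comorbidity and gestational age or prematurity are already named in the protocol, but the timing of the severity items has to be confirmed. Intervals will be wider than the crude ones, and rare outcomes such as death or septic shock will need a penalised model or fewer covariates.

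The alternative is to limit the objectives of these two substudies to description and drop the risk-factor and risk-modifier claims.
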